#### **D.17. Strengths and Limitations:**

**A. Exercise vs health education study -** Our study will be the first trial to examine the efficacy of exercise on QOL and prognosis in ovarian cancer patients. Given differences in disease pathology, prognosis, treatment, and side effects of ovarian cancer vs. breast cancer, it may be unwise to simply generalize results observed from exercise trials in breast cancer patients to ovarian cancer patients. Our trial could suggest a unique and important role for exercise in ovarian cancer care given that physical and functional aspects of QOL are often the most compromised in ovarian cancer patients. There is great potential for our findings to make major changes to clinical practice in ovarian cancer patients. Furthermore, while recent observational studies have shown relationships between physical activity and higher QOL in ovarian cancer patients, the temporality of the relationship is unknown. There are many questions regarding whether ovarian cancer survivors will receive clinically meaningful psychosocial and prognostic benefit from exercise. These questions could best be answered by an adequately powered, individually tailored, randomized controlled trial of exercise vs. control on QOL and prognosis. Thus, our proposed study is innovative and very timely. We have excellent experience and preliminary data in recruiting cancer survivors into exercise trials with high adherence and compliance rates and in measuring physical activity, body composition, quality of life (especially in ovarian cancer survivors), hormones and disease-free survival. Our primary eligibility criterion is that women not be currently exercising at recommended levels. Thus, our proposed intervention is likely generalizable to most ovarian cancer survivors. In summary, we believe that the proposed study will provide important scientific and public health information on an exciting area of ovarian cancer survivorship, and is in keeping with the goals of NCI in finding ways to promote physical activity and improve cancer survival and survivorship.

**Observational study:** All women identified with ovarian cancer throughout CT who do not wish or are not eligible to participate in the exercise study will be invited to participate in this study, making the finding generalizable. The participant burden will be minimal as only a one-time questionnaire.

4. **Statistical Considerations:** Describe the statistical analyses that support the study design.

**Statistical Analyses: Exercise vs. health education study.** We will perform Analysis of Covariance (ANCOVA), with each woman's change in outcome (final value – baseline) modeled as a function of treatment group. Each variable listed in the Primary Aims section above will be examined in this fashion. The hypotheses will be tested according to the intention-to-treat philosophy in which all randomized participants will be grouped according to their intervention assignment at randomization, regardless of compliance or adherence to the study. Secondly, mixed effects models for correlated outcomes will also be used to model the data collected on the absolute change in the outcome measures using all time-point differences. Prior to fitting these models, we will perform exploratory data analyses focusing on the distributions of hormone levels by time and intervention group, assessing the appropriateness of log-transformation. Age, prediagnosis menopausal status, race/ethnicity, baseline BMI, and disease stage will be examined as potential covariates to be included in multi-variable adjusted analyses. Among women randomized to exercise, we will also examine effects of exercise on endpoints stratified by adherence (assessed from the DALs) and other measures of compliance (pedometers and PAQ). To explore the potential for effect modification, we will consider stratifying the effect of exercise on endpoints by menopausal status. Two-sided tests will be used for significance. From the food frequency questionnaires, we will identify participants who change their total caloric intake during the study period, and will assess the effect of exercise on outcomes, controlling for change in total caloric intake. Since we are assessing multiple secondary outcomes, we will consider using Bonferroni correction. Although we do not anticipate an appreciable number of participants lost-to-follow-up because of our plan for tracking participants our plan for missing data handling is as follows. The primary mixed model analyses will be performed using all available data, which assumes missing data are missing at random (86). Under this mechanism, the probability of lost-to-follow-up depends on the observed data. Non-random or informative lost-to-follow-up occurs when there is a correlation between the probability of lost-to-follow-up and missing data.

**Power and Sample Size Considerations:** With a sample size of 230 (which accounts for a potential 30% drop-out/lost to follow up rate) we will have at least 80% power to examine the effect of exercise on QOL and circulating hormones. Our exercise interventions in breast cancer survivors have yielded attrition rates of ~ 10%. Exercise interventions in other cancer survivors (e.g., colon, prostate, and lymphoma) have also yielded similar attrition rates. We hypothesize that attrition may be slightly greater (i.e., 20%) in ovarian cancer patients given their potential for advanced disease, worse QOL and reduced prognosis. However, because no exercise trial has been conducted in ovarian cancer survivors, we now plan to over-recruit to account for a potentially higher attrition rate (30%), and have therefore increased our sample size to N = 230.

In our exercise trial in postmenopausal women, QOL measured by SF-36 was  $79.95 \pm 14.88$  (72). Assuming a 10% effect size, we would need 54 subjects per group or 108 in total. Taking a 30% potential drop-out rate into consideration, then a sample size of 155 is necessary. A 10% between group effect size was observed in Courneya and colleagues recent publication of physical activity and QOL in ovarian cancer survivors (10). A difference of 10 points is clinically meaningful given a recent chemotherapy trial reported an increase of 10 points in QOL, suggesting that 10 points represents a

meaningful improvement in QOL (37). For insulin, Ligibel recently showed a 28% effect size (2.9  $\mu$ U/mL) and standard deviation of 8.0  $\mu$ U/mL, which yields a per group sample size of 80 or total N = 160 (71). Considering the potential for a 30% drop-out with a sample size of 230, a sample size with complete data on 160 women will provide at least 80% power for insulin. For the other hormones, if we assume a 20% effect size, then based on means and standard deviations of these hormones in ovarian cancer survivors (18-20,22,23,47,48,50-55), a sample size of 230 will provide 80% power.

Strategies we will use to achieve a low attrition rate include: 1) Group participant support and communication during the monthly meetings/events; 2) a comprehensive health educational package provided to both groups with weekly topics specifically designed to highlight issues of relevance to ovarian cancer survivors; 3) weekly telephone discussions on topics specific to each participant and their treatment and side effects; 4) quarterly newsletters discussing ovarian cancer health; and 5) incentives. Based on our past experience, and the strategies we will use, we expect a low attrition rate of < 20%.

**Observational study.** We anticipate 80% of the projected 700 women who are invited to participate in the observational study will do so. Analysis will include logistic regression and survival analysis, investigating predictors of survival.

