**Baseline Clinic Visit :** After completion of the baseline visit, in CT the participant will be scheduled (ideally within one week) for a baseline visit at the study center (HRU at YNHH) which will include a DEXA scan to measure total body fat and bone mass and a perometer test to assess leg lymphedema. A binder containing all current IRB approval letters from all participating hospitals will be kept at the

HRU. This can be used by all staff to verify that signed consents from all hospitals are current as some consents are not date stamped.

In Boston the visits will be combined. The participants will also be instructed to fast for 12 hours prior to the visit, not to drink alcohol within 48 hours of the visit, and to refrain from strenuous exercise within 24 hours of the visit. Participants will have ~ 30 ml of blood drawn into 4 vacutainer tubes which will be centrifuged and processed for storage at -70° C as soon as possible following blood draw. Research staff will also review the physical activity and pedometer logs to confirm clarity and completion of the forms. Height, weight, right and left leg circumference and leg length will also be measured.

**D.7B Women enrolled in observational study ONLY (CT residents only):** Among the women screened, but deemed not eligible or interested in participating in the exercise trial, we will invite them to complete a one-time mailed questionnaire (takes ~20 min to complete). One week after mailing the questionnaire, we will follow up with a phone call to confirm receipt of the questionnaire and to answer any questions regarding the study. A stamped, addressed envelope will be provided.

**D.8. Randomization:** Women will be randomized into one of 2 study groups using a random permuted block design of varying block size in a 1:1 ratio (N=115 to intervention, 115 to controls). To ensure women with similar characteristics are equivalently assigned to the 2 groups, we will stratify on menopausal status (at diagnosis) and randomize within each stratum. The following study personnel will be masked to participant study group: staff conducting the baseline interview, conducting the DEXA scan and blood draw, reviewing forms and entering data.

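### The stated ANCOVA names no baseline covariate and gives the randomisation stratum no fixed term, so the analysis as written loses precision

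*Protocol*

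**What the plan says.** Protocol Section 4 (Statistical Considerations, exercise versus health education study) names ANCOVA and describes it as "change in outcome (final value – baseline) modeled as a function of treatment group". It adds that "Each variable listed in the Primary Aims section above will be examined in this fashion", so the form covers quality of life, body composition, serum hormones and salivary cortisol.

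Covariates appear later in the same paragraph: "Age, prediagnosis menopausal status, race/ethnicity, baseline BMI, and disease stage will be examined as potential covariates to be included in multi-variable adjusted analyses". The baseline value of the outcome is not on that list; baseline BMI plays that role only when BMI is the outcome.

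On randomisation, D.8 says "we will stratify on menopausal status (at diagnosis) and randomize within each stratum". In Section 4 that factor appears twice, both times as an option: as one of the potential covariates, and where "we will consider stratifying the effect of exercise on endpoints by menopausal status".

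Section 4 also says that "mixed effects models for correlated outcomes will also be used to model the data collected on the absolute change in the outcome measures". It introduces these as a second analysis, but its missing-data text then calls the mixed models primary. No baseline term is named for them either.

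**The concern.** An analysis of covariance needs a covariate, and the model as written has only treatment group. Taken literally, it is a two-sample comparison of change scores. Subtracting baseline is the same as fixing the coefficient of baseline at 1. An adjusted model estimates that coefficient and is normally more precise for it.

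The variable used to stratify randomisation should also have a settled place in the analysis. If it predicts outcome and is left out, the model's standard error is too large.

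At stake is power, mainly for outcomes with a modest baseline–follow-up correlation and little room in the sample size. The hormones are the likeliest case. An analysis plan that follows the protocol text faithfully would inherit the weaker model.

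**Working it through.** **Inputs.** From Section 4, Power and Sample Size: SF-36 mean 79.95, SD 14.88, a 10% effect, 54 per group, 155 in total after 30% drop-out; insulin difference 2.9, SD 8.0, 80 per group. From D.8: 115 per arm, so 115 × 0.7 = 80.5, about 80 completers per arm. Section 4 specifies two-sided tests. Assumed because the protocol does not give them: alpha 0.05, the correlation r, and equal SDs at the two visits.

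**The plan's own figure.** The quality-of-life effect is 0.10 × 79.95 = 7.995. Then n = 2 × [14.88 × (1.960 + 0.842)/7.995]² = 54.4 per group, against 54 stated. Drop-out: 108/0.7 = 154.3, so 155. Both reproduce. The calculation uses the SD of a score. It matches a change analysis only if 2(1 − r) = 1, that is r = 0.5.

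**General comparison.** Let s0 and s1 be the baseline and follow-up SDs and b = r × s1/s0 the slope of follow-up on baseline. Per woman:

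- change score: s1² + s0² − 2·r·s0·s1
- baseline-adjusted: s1²(1 − r²)
- difference: (s0 − r·s1)² = s0²(1 − b)²

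The difference is never negative and is zero only at b = 1. Apart from the single degree of freedom spent on the slope, the change score never gains and loses unless the slope is 1.

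**Equal SDs.** The ratio becomes 2(1 − r)/(1 − r²) = 2/(1 + r). Simulation with 80 per arm and 4,000 runs gave the inverse ratio as 0.65, 0.74 and 0.88 at r = 0.3, 0.5 and 0.7, against 0.65, 0.75 and 0.85 in theory.

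**Insulin, 80 per group, 8.0 read as a single-visit SD.** The SD is 8.0 × √(2(1 − r)) for change and 8.0 × √(1 − r²) after adjustment. Power by noncentral t:

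| r | Variance ratio | SD, change | SD, adjusted | Power, change | Power, adjusted |
|---|---|---|---|---|---|
| 0.5 | 1.33 | 8.00 | 6.93 | 62.5% | 74.9% |
| 0.6 | 1.25 | 7.16 | 6.40 | 72.2% | 81.3% |
| 0.7 | 1.18 | 6.20 | 5.71 | 83.7% | 89.1% |
| 0.8 | 1.11 | 5.06 | 4.80 | 95.0% | 96.7% |

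If 8.0 is instead the SD of change, unadjusted power is about 63% whatever r is. Adjustment multiplies the variance by (1 + r)/2 and gives about 81%, 75% and 70% at r = 0.3, 0.5 and 0.7.

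**Quality of life, 80 per group.** At r = 0.3 the change SD is 14.88 × √1.4 = 17.61. Power is 81.9% on change and 94.5% adjusted (normal approximation; noncentral t gives 81.4% and 94.3%). At r = 0.5 the normal approximation gives 92.5% and 97.5%.

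**Chance imbalance.** This is the same loss seen in a single trial. A one-standard-error baseline difference in insulin is 8.0 × √(2/80) = 1.26. With b = 0.5, change and adjusted estimates differ by (1 − 0.5) × 1.26 = 0.63, or 0.63/2.9 = 22% of the target difference.

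**Stratum term.** If menopausal status explains a share R² of the residual variance, omitting it inflates the model standard error by 1/√(1 − R²): 1.005 at R² = 0.01 and 1.054 at R² = 0.10. That R² range is assumed.

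**The case against.** The word ANCOVA may be shorthand for a baseline-adjusted model of change, with the exact terms left to an analysis plan that is not shown. This stands in part: nobody can conclude that the sponsor means to exclude baseline. But the protocol is not silent. It writes out a model and a covariate list, and baseline is in neither. Label and formula disagree, and that needs resolving.

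Four stronger readings are tempting and not supported.

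- A reader might infer bias. Randomisation keeps the change contrast unbiased on average.
- A reader might infer that a change score over-corrects whenever r is below 1. The slope decides, not r. With r = 0.8 and a follow-up SD 1.25 times the baseline SD, b = 1 and the two analyses tie.
- A reader might infer that this choice leaves insulin underpowered. At r = 0.7, with 8.0 as a single-visit SD, change already gives 84%. Section 4 does not say which SD 8.0 is. Whether 80 per group is right for insulin is a separate question.
- A reader might infer that covariates of the main model will be picked from the data. Section 4 attaches the optional list to multi-variable adjusted analyses, apart from the model of change on arm.

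It is also fair to say that quality of life is well protected, that the stratum term matters little, and that omitting it errs on the conservative side.

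**Conclusion.** The point holds as one of efficiency and pre-specification. As written, both candidate primary analyses model change with no baseline term, so it stands whichever is primary.

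Under equal SDs the excess variance is 33% at r = 0.5, 18% at 0.7 and 11% at 0.8. Adjusting would need 25%, 15% or 10% fewer women for the same power. These figures rest on assumed values of r, because the protocol gives none.

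For insulin the loss is about 12 percentage points of power at r = 0.5, 9 at 0.6 and 5 at 0.7 if 8.0 is a single-visit SD. Quality of life keeps about 80% power or more on change for r of 0.3 or above. Nearly all the gain comes from the baseline outcome. The stratum belongs in the model mainly because randomisation used it. The change should be made, but its absence does not threaten validity.

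**What to change.** First state which analysis is primary, the ANCOVA or the mixed model. For that model, specify: follow-up value (or change) = arm + baseline value of the same outcome + menopausal status at diagnosis, with both terms always included whatever their significance. Put baseline on the same scale as follow-up, so that if a hormone is log-transformed, its baseline is too. In a mixed model with more than one follow-up visit, baseline and stratum enter as covariates in the same way. Use the same specification for the analysis that is not primary.

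Move age, race/ethnicity, baseline BMI and disease stage to one sensitivity model listed in advance. When BMI is the outcome, its baseline value is already in the main model.

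The cost is a sentence or two in the protocol or analysis plan and one or two degrees of freedom. The protocol already plans to collect the baseline outcomes and the stratum.

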### **D.3A. Study Population for Exercise Trial:**

#### **Table D.1: Study Inclusion and Exclusion Criteria**

##### **Inclusion Criteria:**

- Ages 18-75 years at the time of the screening phone call
- AJCC Stages I-IV invasive epithelial ovarian cancer
- Completed adjuvant therapy (i.e. chemotherapy (platinum and a taxane) and/or radiation therapy) at least one month prior to randomization
- Diagnosed within the past four years
- Physically able to exercise and physician consent given to start an exercise program
- Sedentary activity pattern (< 90 mins/week of moderate-to-vigorous intensity recreational physical activity)
- Agrees to be randomly assigned to either of the exercise or the health education group
- Gives informed consent
- Able to travel to New Haven for a baseline and a six-month visit
- Accessible by telephone
- English speaking

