##### **Exclusion Criteria:**

- Recent (past 6 months) stroke or myocardial infarction

While physical activity may improve QOL several years after diagnosis, we have limited our eligibility to women diagnosed within the past 3 years because of wanting to recruit a somewhat

homogenous sample of women, i.e., women who survive five or more years may differ from women who do not, and the relationship between physical activity, QOL, and prognosis may also differ.

Women must have completed all chemotherapy and radiation at least one month prior to enrollment so that both baseline and follow-up blood analysis are not confounded by whether or not women were receiving chemotherapy.

To observe a maximal effect from the exercise intervention, only women reporting less than 90 min/wk of moderate-to-vigorous intensity sports/recreational physical activity will be eligible for the study. National prevalence data on physical activity indicate that more than three-quarters of American adults report no exercise activity whatsoever. Thus omitting physically active women would not appreciably limit our generalizability. Women with lower average levels of activities, such as in household or occupational settings, even of long durations, would still be eligible. However for all women we will examine eligibility on a per case basis with respect to ability to walk. In summary, our primary exclusion criteria include highly physically active women; thus, we feel our study will be generalizable to most ovarian cancer survivors.

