### **Study enrollment**

We will mail an invitation letter to the participant, describing the study and telling her that one of the study staff will be contacting her within a week to tell her about the study and to solicit her interest and eligibility. If the participant is eligible and interested, a baseline visit will be scheduled either in the subject's home or in the study office. At this point, the physician will also be contacted again via letter to solicit permission for the participant to participate in a monitored, moderate-intensity exercise program. If the participant is currently undergoing chemotherapy, she will be told that she will be called back approximately one month after her chemotherapy has ended. If eligible, women who contact study staff without having received a letter of invitation (women who picked-up a brochure at their clinician's office, or who heard of the study through friends, survivorship support groups, the media etc.) will be randomized following receipt of written permission to exercise from their MD, as with those contacted through the RCA mechanism. To reach more eligible women, we will include information about the study on appropriate internet sites, such as the 'Love/Avon Army of Women recruitment for your study' site.

Our goal is to recruit 230 ovarian cancer survivors over 3.5 years. As mentioned, we will approach approximately 1,250 ovarian cancer survivors for the study to randomize 230 women. Prior pilot studies, performed at Yale, of exercise interventions in cancer survivors, or QOL studies in ovarian cancer survivors have response rates of 15-65%. These rates suggest that our recruitment goals are feasible. Specifically, if we assume 90% survival to recruitment, 95% physician consent, and 75% eligibility, 641 women will be approached for interest of which roughly the first 230 agreeing will be randomized. These rates are based on results from our previous cancer studies, and show that our recruitment is feasible. Even though a subject participation fraction of 35% may be considered on the low side for an epidemiologic investigation, in a randomized controlled trial the first consideration is internal validity, which is generally assured by the randomization. Generalizability could be somewhat less certain, however we will have pathology information and ultimately survival data on essentially all eligible subjects and will be able to compare participants with nonparticipants.

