**Salivary cortisol:** Women will be asked to collect 2 saliva samples (wake up and bedtime) for 4 days prior to the baseline clinic visit and the final clinic visit. Analysis of samples will be conducted at YCCI.

**Tumor specimens:** At baseline, we will request consent from the participants to obtain tumor specimens for future ancillary studies relating to ovarian disease, including investigating the role of tumor characteristics in the prognosis of ovarian disease.

**D.11. Medical Record Abstraction and Physician Verification of Treatment Reports:** The following will be obtained via a Physician Verification of Treatment Report or abstraction from the medical records: clinical stage, therapy received (chemotherapy/surgery/radiation) and treatment dates.

**D.12.A Exercise Intervention:** Given the primary side effect of ovarian cancer surgery and treatment is fatigue, and given exercise has had a favorable impact on fatigue in breast cancer survivors, we hypothesize that a similar intervention adapted for ovarian cancer survivors will increase physical activity levels, and this increase in activity will have a favorable impact on fatigue, QOL and surrogate markers of survival. However, given that another symptom reported by ovarian cancer patients may include peripheral neuropathy, we will individualize and modify the exercise program based on any special needs secondary to surgery and treatment (e.g., if the participant is experiencing peripheral neuropathy, then we will recommend supervised exercise at the gym or recommend other activities such as swimming, stationary recumbent bicycling and/or upper body ergometry). The exercise program will also be individualized based on the participant's history of participation in physical activity and her preferred type of exercise.

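### Time since last treatment is neither a stratifier nor a named covariate for a six-month change outcome, which costs a modest amount of precision that dates already collected could recover

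*Protocol*

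**What the plan says.** **Entry window.** Table D.1 in section D.3A requires adjuvant therapy to have ended "at least one month prior to randomization". Its upper limit is "Diagnosed within the past four years", but the text below the table says "we have limited our eligibility to women diagnosed within the past 3 years". These two must be reconciled; the present point holds under either. Under Study enrollment, a woman still on chemotherapy when contacted is not lost: "she will be told that she will be called back approximately one month after her chemotherapy has ended".

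**Randomization (D.8).** The only stratifier is menopausal status: "we will stratify on menopausal status (at diagnosis) and randomize within each stratum".

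**Analysis (section 4).** The model is an ANCOVA "with each woman's change in outcome (final value – baseline) modeled as a function of treatment group". For the multivariable analyses, "Age, prediagnosis menopausal status, race/ethnicity, baseline BMI, and disease stage will be examined as potential covariates". Neither this list nor the questionnaire covariates in D.10.A (item 8) contains time since treatment or time since diagnosis.

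**Data (D.11).** The record abstraction or physician report supplies "therapy received (chemotherapy/surgery/radiation) and treatment dates", so time since last treatment can be derived.

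**The concern.** A woman randomized one month after chemotherapy is observed from about month 1 to month 7 after treatment. Another may be observed over six months that begin years later. If quality of life, fatigue or blood markers change at different natural rates in these two periods, part of the spread in six-month change reflects where a woman stands after treatment and not the exercise programme.

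The protocol itself gives reason to think time matters. Its background says that fatigue goes on after treatment ends, and that neuropathy may last for months or become permanent, though perhaps less severe. It limits time since diagnosis to obtain a more homogeneous sample. It also cites an observational study of 359 survivors in which a more recent diagnosis went with lower activity. The one-month gap is justified only by the wish to avoid blood taken during chemotherapy, which does not deal with recovery afterwards.

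What is at stake is precision, together with a chance imbalance between the arms in a factor that readers will ask about. If the covariate is first added after the results are known, it will look data-driven.

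**Working it through.** **Inputs from section 4 (Power and Sample Size Considerations):** SF-36 mean 79.95 and SD 14.88; 10% effect, so 0.10 × 79.95 = 7.995 points; 80% power; 30% dropout; N = 230; insulin difference 2.9 with SD 8.0 and 80 per group. Tests are two-sided. The alpha level is not stated, so 0.05 is assumed.

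**Input not in the documents:** R², the share of outcome variance explained by time since last treatment. The assumed range is 1% to 15%.

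**1. The plan's own figure.** n per group = 2 × [14.88 × (1.960 + 0.842) / 7.995]² = 54.4, or 55 rounded up, against 54 stated. With dropout, 108 / 0.70 = 154.3, rounded up to 155 as stated. N = 230 leaves 230 × 0.70 = 161 completers, about 80 per group.

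**2. Effect of adjustment on quality of life.** Residual SD = 14.88 × √(1 − R²). With 80 per group the unadjusted standard error is 14.88 × √(2/80) = 2.35. Power is Φ(7.995/2.35 − 1.96) = 92.5%, and the 95% half-width is 1.96 × 2.35 = 4.61 points. The adjusted half-width is 4.61 × √(1 − R²).

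| R² | n per group for 80% power | Power at 80 per group | 95% half-width (points) |
|---|---|---|---|
| 0 | 55 | 92.5% | 4.61 |
| 1% | 54 | 92.7% | 4.59 |
| 5% | 52 | 93.7% | 4.49 |
| 10% | 49 | 94.8% | 4.37 |
| 15% | 47 | 95.8% | 4.25 |

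The saving is 1 to 8 women per group, and the half-width narrows by about 0.02 to 0.36 points.

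**3. Chance imbalance.** With 80 per group, the standardised difference between arms in any baseline factor has standard error √(2/80) = 0.158, so 95% of randomizations fall within ±1.96 × 0.158 = ±0.31 SD. At that limit the unadjusted quality-of-life difference shifts by √R² × 0.31 × 14.88:

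- R² = 1%: 0.5 points (6% of 7.995)
- R² = 5%: 1.0 points (13%)
- R² = 10%: 1.5 points (18%)

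**4. Insulin.** From the protocol's own inputs, 80 per group gives standard error 8.0 × √(2/80) = 1.265 and power Φ(2.9/1.265 − 1.96) = 63%. (That the stated 80 per group does not reproduce is a separate matter; the two-sided formula gives 120.) An R² of 10% would raise this power to about 68%, and 15% to about 70%. Precision is therefore worth more here than for quality of life.

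**The case against.** **The list is open, and a statistical analysis plan could extend it.** True: the five factors are only candidates. But the protocol chose to name them, and it left out a factor that its own background and eligibility reasoning bring forward.

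**Validity is not at issue.** This stands in full. A reader might infer that uneven recovery biases the exercise effect or inflates type I error. It does not, because randomization protects the unadjusted test and its standard error already allows for the variation. The shifts in step 3 are part of that standard error, not an extra error on top of it.

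**The gain is small and rests on an assumption.** This also stands. Quality-of-life power is already about 92.5% at 80 per group. The documents give neither R² nor the share of women who enter soon after treatment; the call-back rule shows that early entry happens, not how often. The SD of 14.88 comes from a trial in postmenopausal women and is not stated to be an SD of change. If the ANCOVA also includes the baseline score, that may absorb part of the gain.

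**The recovery pattern is not documented.** The background describes symptoms that persist as much as symptoms that resolve. Relevance is plausible, not shown.

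**Three further readings go too far.** The three- or four-year limit runs from diagnosis, so it overstates the possible spread in time since treatment. The treatment dates cannot be called unused, since they have an evident role in checking eligibility. Recruitment site might seem to call for the same adjustment, but the protocol gives no out-of-state numbers and nothing from which to size an effect, and telephone counselling is the main means of delivery.

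**Conclusion.** The point holds as a modest precision matter. A plausible prognostic factor for six-month change is absent from both the stratification and the named covariates, while the dates needed to derive it are collected. For quality of life the benefit of adjusting is a few women per group, and at most about 3 points of power if R² is 15% or less. For insulin it could be about 5 points of power at R² = 10%, from a base of only 63%. All of this depends on the assumed R², on a two-sided alpha of 0.05, and on the protocol's planning SDs applying to the change analysed. The trial's validity is not in doubt.

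**What to change.** In section 4, Statistical Analyses, add time from the end of last adjuvant treatment to randomization, derived from the D.11 dates, as a pre-specified covariate in the adjusted primary-aim models and not merely as one more candidate to be examined. Fix its form before any outcome is compared by arm: log scale, or categories with stated cut-points. State how a missing treatment date will be handled.

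The cost is about one degree of freedom for the log term or a two-level category, and a sentence or two of text. Stratification, data collection and participant contact do not change.
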